## 14.3 Interim analysis and data monitoring

### Green/Amber/Red Criteria for recommending a full RCT

As this is a pilot trial, there will be no interim analysis. Rather, the TSC review at the end of the pilot trial will serve as data monitoring, as part of the overall decision about whether to proceed with a substantive trial. All unexpected serious adverse events will be reported to the TSC, and the TSC will have the power to pause the trial to assess unblinded data if that appears necessary for ensuring participants’ safety, as well as the power to stop the trial if participants’ safety appears to be at risk.

The following will be used to determine the feasibility of comparing standard care versus OptiBreech care:

A = total number of women randomised to OptiBreech VBB care

B = number of women declining OptiBreech VBB care in favour of ECV or CS first

C = total number of women randomised to ECV / standard care

D = number of women declining ECV attempt in favour of VBB or CS first

E = number of women lost to follow-up

F = number of sites participating in OptiBreech 2

G = number of months to achieve 104 recruits

H = number of sites in OptiBreech 1 meeting requirements for participation

J = number of additional sites indicating interest in joining the trial

Total women required for randomisation: 2280 to compare the outcome of ‘neonatal admission’ using current evidence on incident rates

48 women / month for 48 months

Green for trial: ($\frac{\left( A-B \right)+\left( C-D \right)-E}{F(G)})*(F+H)$ > 48 women

Amber: ($\frac{\left( A-B \right)+\left( C-D \right)-E}{F(G)})*(F+H+J)$ > 48 women

Red: ($\frac{\left( A-B \right)+\left( C-D \right)-E}{F(G)})*(F+H+J)$ < 48 women

For example:

104 women (A+C) are recruited by 5 months (G = 5)

52 are randomised to OptiBreech care (A = 52) but 30 decline this in favour of ECV or CS (B = 30)

52 are randomised to ECV (C = 52) but 20 decline this in favour of CS or VBB (D = 20)

2 women are lost to follow-up (E = 2)

5 sites participated in OptiBreech 2 (F = 5)

10 more sites in OptiBreech 1 are meeting participating criteria (H = 10)

25 more sites not currently participating have expressed an interest (J = 25)

($\frac{\left( A-B \right)+\left( C-D \right)-E}{F(G)})*(F+H)$ = 31.2

($\frac{\left( A-B \right)+\left( C-D \right)-E}{F(G)})*(F+H+J)$ = 83.2

The feasibility trial will meet the Amber light criteria. Depending on the number of sites who are able to develop their service enough to meet the criteria, it should be feasible to compare standard care with OptiBreech VBB care in a randomised trial delivered within 48 months.

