| Main Inclusion Criteria |  | **Cohort:**   - Breech presentation >32 weeks of pregnancy, referred for specialist care related to breech presentation - Breech presentation >37 weeks of pregnancy discovered in labour - Requesting or preferring a vaginal birth, with no absolute contraindication   **Trial within cohort:**   - no relative contraindication associated with higher risk of vaginal breech birth or ECV - no indication for induction prior to 41 weeks at the time of recruitment |
| Statistical Methodology and Analysis |  | Descriptive statistics will be used to report recruitment and adherence rates. The feasibility study is not powered to detect a difference in safety, but at its conclusion, all SAEs and safety outcome measures will be reviewed by the Trial Steering Committee. |

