## Ethics Reporting

Reports of related and unexpected SAEs will be submitted to the Main REC within 15 days of the CI becoming aware of the event, using the NRES template. A copy of the SAE notification and acknowledgement receipt will be sent to the R&D Directorate.

Maternal or neonatal deaths, and admissions to the NICU for longer than 4 days should be reported immediately to the CI as SAEs.

The following neonatal SAEs are expected and should be recorded and reported according to the protocol:

| Admission to the NICU for up to 4 days  Low Apgar score  Low cord blood gases  Neonatal resuscitation  Hematoma  Haemorrhage  Spinal cord injury  Skull fracture  Bone fracture  Peripheral nerve injury/Brachial plexus injury present at discharge from hospital  Facial nerve paresis  Significant genital injury  Laceration to baby buttocks  Respiratory distress syndrome requiring treatment  Neonatal seizures or convulsions  Neonatal encephalopathy  Necrotizing enterocolitis  Perinatal infection  Neonatal hypoglycemia requiring treatment  Hyperbilirubinemia / neonatal jaundice requiring treatment  Stupor/decreased response to pain/coma  Facial palsy |
| --- |

The following maternal SAEs are expected and should be recorded and reported according to the protocol:

Haemorrhage

Obstetric Anal Sphincter Injury (OASI)

Admission to higher-level care for up to 4 days

Cervical laceration involving lower uterine segment

Vertical uterine incision or serious extension to transverse uterine incision

Bladder, ureter or bowel injury requiring repair

Dilation & curettage for bleeding or retained placental tissue

Manual removal of placenta

Uterine Rupture

Hysterectomy

Vulval or perineal haematoma requiring evacuation

Wound dehiscence / breakdown

Wound infection requiring prolonged hospital stay / readmission / antibiotics

Sepsis

Disseminated Intravascular Coagulation

Re-admission within 28 days following birth

Table 4: Information with regards to Safety Reporting

|  | **Who** | **When** | **How** | **To Whom** |
| --- | --- | --- | --- | --- |
| **SAE** | Chief Investigator | -Report to Sponsor within 24 hours of learning of the event  -Report to the MREC within 15 days of learning of the event  - Report to TSC within 15 days of learning of the event | SAE Report form for Non-CTIMPs, available from NRES website. | Sponsor, MREC and TSC |

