## Trial Steering Committee (TSC)

The role of the TSC is to provide the overall supervision of the study. All SAEs and details will be reported to the TSC and Sponsor and REC when relevant as directed by the TSC. The TSC will monitor the progress of the study and conduct and advise on its scientific credibility. In this early stage of feasibility testing, the TSC will also fulfil the role of a Data Monitoring Committee and include an independent statistician. The TSC ultimately carries the responsibility for deciding whether a substantial trial is feasible.

A TSC charter will be agreed at the first TSC meeting to document how the committee will operate.

Members of the TSC are as follows:

[name] (Chair)

[name]

Statistician: TBA

[name], London, Service User

[observer from the NIHR]

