## Meeting schedule

One meeting will occur in the first three months of study opening, to review accumulated data from OptiBreech 1, prior to the start of randomisation in this study. Another meeting will occur after the close of recruitment. Following the meeting, a report and recommendation regarding the feasibility of conducting a full RCT will be submitted to the Sponsor.

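### The data-monitoring section limits SAE reporting to the TSC to unexpected events, whereas the oversight section and Table 4 send the TSC all SAEs

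*Protocol*

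**What the plan says.** Three places in the protocol state which SAEs go to the TSC.

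- **Interim analysis and data monitoring** (under the Green/Amber/Red criteria): "All unexpected serious adverse events will be reported to the TSC". The same sentence gives the TSC its power to pause the trial, look at unblinded data and stop the trial.
- **Study Oversight Arrangements, Trial Steering Committee (TSC)**: "All SAEs and details will be reported to the TSC and Sponsor and REC when relevant as directed by the TSC".
- **Assessment of safety, Table 4**, row for SAEs, with no filter on expectedness: "Report to TSC within 15 days of learning of the event".

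The Ethics Reporting section defines what counts as expected through two lists, introduced by "The following neonatal SAEs are expected and should be recorded and reported according to the protocol" and "The following maternal SAEs are expected and should be recorded and reported according to the protocol".

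On timing, the data-monitoring section plans no interim analysis and treats the TSC's review at the end of the pilot as the data monitoring. The meeting schedule has one meeting before randomisation starts, and then "Another meeting will occur after the close of recruitment". The Summary adds that, at the study's conclusion, "all SAEs and safety outcome measures will be reviewed by the Trial Steering Committee".

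For the REC, the Ethics Reporting text says "Reports of related and unexpected SAEs will be submitted to the Main REC within 15 days".

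**The concern.** The same duty, what the TSC is told about SAEs, is stated with two different scopes. The narrower one stands where the stopping power is granted. The qualifier has little purpose unless it limits what is sent.

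The limit would remove a great deal. The expected lists include spinal cord injury, skull fracture, seizures, encephalopathy, uterine rupture, hysterectomy, sepsis and disseminated intravascular coagulation. In this pilot the TSC is also the data monitoring committee. Between its two scheduled meetings, SAE notices are the only safety information that the protocol specifies for it. The TSC may call an ad hoc meeting at any time, but over concerns that arise from safety reporting, so that safeguard depends on the same notices. A site or trial office working from the data-monitoring section would send the TSC a filtered feed for the whole randomisation period.

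**Working it through.** The protocol states no figure to reproduce here. The check compares the texts and adds two counts.

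**1. Scope by recipient**

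| Place in protocol | To the TSC | To the REC |
|---|---|---|
| Interim analysis and data monitoring | unexpected SAEs | not stated |
| Oversight, TSC section | all SAEs | when relevant, as the TSC directs |
| Table 4, SAE row | any SAE, 15 days | any SAE, 15 days |
| Ethics Reporting, text | not stated | related and unexpected SAEs, 15 days |

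The TSC has two scopes and the REC has three.

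**2. How much of the protocol's serious morbidity is expected**

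Inputs: the components of the neonatal and maternal composites (Secondary Outcomes, items 3 and 4) and the expected lists in Ethics Reporting (22 neonatal and 16 maternal items). Components are matched by name. The lists are often broader than the components: low Apgar, haemorrhage and convulsions carry no threshold there.

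- Neonatal composite, 8 morbidity components. Matched: low Apgar score, peripheral nerve injury, skull fracture, spinal cord injury, convulsions = 5. Unmatched: NICU stay over 4 days, ventilation over 24 hours, parenteral or tube feeding over 24 hours = 3.
- Maternal composite, 14 morbidity components. Matched: 14.
- Morbidity components: (5 + 14) / (8 + 14) = 19/22 = 86%.
- Adding the two death components, neither of which is listed as expected: 19/24 = 79%.

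**3. What the narrower sentence would still send**

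Maternal and neonatal deaths and NICU stays over 4 days are absent from the expected lists and are singled out for immediate report to the chief investigator. Prolonged ventilation and prolonged tube feeding, maternal higher-level care beyond 4 days and stillbirth are not listed as expected either. None of these is excluded by the qualifier.

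**4. Illustration of size**

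Inputs: 104 randomised women (Summary; Sample size calculation) and a background neonatal admission rate of 5-7% at term (Assessment of safety).

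- 104 × 0.05 = 5.2
- 104 × 0.07 = 7.3

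So about 5 to 7 admissions are expected over both arms. Stays of up to 4 days are listed as expected and fall outside the data-monitoring sentence; longer stays do not. The protocol gives no split by length of stay, so the number affected cannot be fixed more closely than between none and all of these. The 104 randomised women are the right base because the question is monitoring during randomisation. The non-randomised cohort of about 50 is only an estimate and includes OptiBreech 1 women entered retrospectively.

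**The case against.** The strongest reply is that the narrower sentence does not say 'only'. Reporting all unexpected SAEs is a subset of reporting all SAEs, so the sentence can be read as incomplete rather than conflicting. The two places whose purpose is to set reporting, Table 4 and the TSC section, are both unfiltered. Expected SAEs must themselves be reported according to the protocol, which leads back to Table 4. The likely intent is therefore full reporting, and the defect is one loose adjective in a section mainly about progression criteria. This reading of the intent stands. It does not remove the need to correct the text, because the adjective qualifies the reporting attached to the stopping power.

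A reader might go further and infer that the committee acting as data monitoring committee is left without the safety data. The documents do not support that. Two sections send it all SAEs. The Summary and the data-monitoring section provide for a review at the end. The TSC's independent statistician is to receive all original data, although no timing is given. The TSC can meet ad hoc, and its charter, to be agreed at the first meeting, is not shown. The gap is conditional on the narrower sentence being followed, and it concerns only the period of the trial.

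It is also fair to say that, with about 5 to 7 admissions over two arms, a difference between arms would be hard to see even with full reporting; the protocol says that the study is not powered for safety. That limits what any feed could reveal statistically. It does not lessen the value of individual notices of severe injury.

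**Conclusion.** The contradiction is real and lies in the protocol's own text. As written, the data-monitoring section gives the TSC a narrower SAE feed than the oversight section and Table 4. If it were followed, most of the protocol's own serious morbidity (19 of 22 components) would not be sent to the TSC during randomisation, while deaths, NICU stays over 4 days and other unlisted events still would be.

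This rests on two assumptions: that the Ethics Reporting lists decide what is expected, and that the qualifier is meant to limit scope. No sample size, power or analysis figure is affected. The REC scope has the same kind of inconsistency, with three different rules. The point is a moderate one: the intended rule is probably already in the document, but the section that holds the stopping power says otherwise.

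A reader might also conclude that the protocol must provide cumulative counts by arm. Neither the oversight section nor Table 4 contains such a requirement, and the inconsistency does not create one.

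**What to change.** Delete 'unexpected' from the data-monitoring sentence so that it agrees with the TSC section and the SAE row of Table 4: all SAEs go to the TSC, within the 15 days that Table 4 already sets.

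In the same edit, reconcile the REC scope across the Ethics Reporting text, Table 4 and the TSC section, so that each recipient has one stated scope and time limit.

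The cost is wording only. The reporting line to the TSC already exists in Table 4, and no new data, meeting or analysis is needed.

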Breech presentation occurs in 4% (1:25) of term pregnancies.^16^ As many as 35-58% of women may prefer to plan a breech birth, but this is highly dependent on the type of counselling they receive.^18,19^ Yet a 2014 survey of UK maternity units found that only 27% offered support for a vaginal breech birth.^20^ Some hospitals have created breech clinics and/or an on-call team to revive breech skills;^21,22^ these attract women who lack local support.^23,24^ In some hospitals, the vaginal breech birth rate can be as high as 6-11% of the total birth rate due to women travelling to experienced providers,^23,24^ compared to 0.4% of the total birth rate in the UK.^25^ This suggests inequity and demand for skilled breech birth care.

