Consent will ideally be a research midwife, but because consent is taken prior to the start of their breech care pathway, it can be taken by any healthcare professional who has completed GCP training or OptiBreech GCP-lite training and signed the delegation log. When women are enrolled, they will be given login information so that they can enter their details directly onto the database. These login details will later be used to complete the follow-up surveys if women have consented to receive these. Consent will be confirmed on-line by the health care professional who has taken consent. Paper copies of the PIS and Consent forms will be provided in case the on-line version fails or is inaccessible.

A copy of the consent form will be sent to the woman and local research team, to be filed in the woman’s notes. Where paper-based consent forms have been used, a scanned copy should be sent by secure electronic transfer or encrypted NHS e-mail to the core research team.

PPI work indicated that enabling women to access participation in this study if they wish was a priority. All PPI group participants had experience of either their own difficulty seeking support for a vaginal breech birth, or experience of supporting women who were having difficulty accessing care for a vaginal breech birth. Additionally, approximately 1/3 of the participants in OptiBreech 1 were self-referrals, who transferred care from another Trust to receive support for a vaginal breech birth within a hospital participating in OptiBreech 1. Therefore, if a Trust feels it is ready to accept self-referrals, contact information for their Breech Clinic will also be made available via the study’s website, for women who may wish to self-refer. Women may self-refer either internally or from a different Trust if they would like to participate in the research. In this case, women would be screened by OptiBreech staff for suitability.

The minimum recruitment target for each site in this 6-month pilot trial is 10 women who consent to randomisation. Each additional recruitment to the cohort study (non-randomisation) will count as an accrual, but the minimum recruitment target is based on women who consent to randomisation.

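### The Green/Amber/Red rule scales a per-site rate that includes women transferring from other Trusts, so the projection can be inflated and an Amber value just above 48 could be Red

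*Protocol*

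**What the plan says.** The section on Green/Amber/Red criteria (Protocol, 14.3) defines the two main inputs as "A = total number of women randomised to OptiBreech VBB care" and "C = total number of women randomised to ECV / standard care". Neither is restricted by how the woman reached the site. The rule subtracts decliners in each arm (B, D) and losses to follow-up (E), then divides by pilot sites times months (F × G). For Green it multiplies by F+H, where H is OptiBreech 1 sites meeting the requirements. For Amber and Red it multiplies by F+H+J, where J is further interested sites. The threshold is 48 women per month, from 2280 women over 48 months.

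The section on participant recruitment opens the study to women from elsewhere, where a Trust is ready to accept self-referrals: "Women may self-refer either internally or from a different Trust if they would like to participate in the research". It also reports that "approximately 1/3 of the participants in OptiBreech 1 were self-referrals, who transferred care from another Trust to receive support for a vaginal breech birth". Nothing in the progression criteria, or in the paragraph interpreting the worked example, adjusts for this.

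**The concern.** The rate is measured at a few sites and projected onto many. The section on sites says that randomisation starts in 2 Trusts (3 hospitals). The introduction says that two Trusts, with three hospitals between them, recruited 21 of the 27 OptiBreech 1 women and were the only ones then meeting the inclusion criteria. Such sites can attract women whose own Trust offers no comparable service.

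The worked example goes from 5 sites to 40. Holding the inflow per site constant would need eight times as many travelling women, while 35 further sites open and reduce the need to travel. A woman recruited at her home Trust cannot also be counted as a transfer elsewhere. Even if her home Trust never joins, the same pool of travellers is shared among more sites.

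This matters because the rule is the protocol's stated basis for judging whether a full trial is feasible. The exposure is greatest on the Amber line, which has the largest multiplier.

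**Working it through.** **Inputs** (worked example in the Green/Amber/Red section): A = 52, B = 30, C = 52, D = 20, E = 2, F = 5, G = 5, H = 10, J = 25; threshold 48 (2280/48 = 47.5, rounded up). The transfer share s among randomised women is not stated. I assume 1/3 (the OptiBreech 1 figure) and 10% for illustration.

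**The plan's own figures.** Net count = (52 − 30) + (52 − 20) − 2 = 52. Rate r = 52/(5 × 5) = 2.08 women per site per month.
- Green expression: 2.08 × 15 = 31.2.
- Amber expression: 2.08 × 40 = 83.2.

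Both match the protocol, which reads the example as Amber.

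**Removing transfers.** Two versions, with s the share of the net count:
- (a) at all sites: r(1 − s) × number of sites;
- (b) at added sites only: rF + r(1 − s)H for Green, rF + r(1 − s)(H + J) for Amber.

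| s | Green (a) | Amber (a) | Green (b) | Amber (b) |
|---|---|---|---|---|
| 0 | 31.2 | 83.2 | 31.2 | 83.2 |
| 10% | 28.1 | 74.9 | 29.1 | 75.9 |
| 1/3 | 20.8 | 55.5 | 24.3 | 58.9 |

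At s = 1/3 the Amber figure under (b) is 2.08 × 5 + 2.08 × (2/3) × 35 = 10.4 + 48.5 = 58.9.

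**When the colour changes.** Under (a) a displayed Amber value falls below 48 if it lies between 48 and 48/(1 − s):
- s = 1/3: 48 to 72.
- s = 10%: 48 to 53.3.

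With the other example inputs kept and s = 1/3, that means J = 9 to 19 under (a), displayed as 49.9 to 70.7. Under (b) it means J = 9 to 17. The example itself (J = 25) turns Red only if s exceeds 1 − 48/83.2 = 42.3% under (a), or 1 − (48 − 10.4)/72.8 = 48.4% under (b).

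**Check on applying s to the net count.** Suppose 1/3 of the 104 randomised women (34.7) are transfers, split equally between arms, who all accept OptiBreech care and all decline ECV. They contribute 17.3 to the net count, which falls to 34.7, and 34.7/25 × 40 = 55.5, the same answer. If they accepted whichever arm they were given, the net count would be 17.3 and the Amber figure 27.7 (Red). That is an extreme case for women who travelled to obtain a vaginal breech birth.

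**Offset from subtracting decliners.** The 2280 is a number to be randomised, yet the rule removes B and D. Without that subtraction the Amber expression is (104 − 2)/25 × 40 = 163.2, and 108.8 after removing one third. The Green expression is 4.08 × 15 = 61.2, and 40.8 after removing one third. Both reduced values remain above the rule's own 83.2 and 31.2.

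**The case against.** The strongest objection is that one third belongs to a different population. The sample size section says that OptiBreech 1 drew only on women already wanting a vaginal breech birth, whereas the pilot invites all eligible women. Several provisions point to a lower share among those randomised:
- a prior ECV attempt excludes from randomisation;
- the screening section describes transfers after failed ECVs elsewhere;
- site requirements call for a plan to recruit straight after the diagnostic scan, before counselling on ECV or mode of birth;
- a woman who travelled for a breech birth can decline randomisation and join the cohort only.

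All of this stands. It limits the size of the bias, not its direction.

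Removing every transfer also over-corrects. No passage says that the home Trusts are among the H or J sites. Women from non-participating Trusts could still transfer and would be valid recruits in a full trial. This stands too, and is why version (b) and a range are preferable to a single deflated figure.

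A reader might cite the introduction's remark that at some hospitals "the vaginal breech birth rate can be as high as 6-11% of the total birth rate due to women travelling to experienced providers". That shows women travel for the service, but it is a birth rate, not a rate of consent to randomisation, and cannot size the effect. A reader might also infer a separate distortion through B and D. The rule sums the two arms, and women who accept OptiBreech care and decline ECV move B and D in opposite directions; the count-based check gives the same 55.5, so no further bias is shown.

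Finally, the rule is not mechanical. Amber is made conditional on sites developing their services, the steering committee decides, and its independent statistician receives the data. But the protocol asks nobody to look at referral route, so this lessens the risk without removing it.

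**Conclusion.** The concern holds in conditional form. The rule scales a rate that includes transfers onto sites that are unlikely to receive them at the same rate, so the projection can be inflated and an Amber value just above 48 could be Red. The size rests on an unknown. If one third carried over and transfers were removed at all sites, the band at risk would be 48 to 72; at 10% it would be 48 to 53.

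Two stronger readings are not supported. One is that the protocol's example is really Red: at one third it stays Amber, at 55.5 or 58.9. The other is that the projection is too high overall: the transfer share among randomised women is not given, and subtracting decliners pushes the projection down, so net inflation against 2280 is not shown. That offset is a separate feature of the rule and does not make the per-site rate portable. This is an inexpensive improvement to the decision rule, not a flaw that invalidates the pilot.

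**What to change.** In the Green/Amber/Red section:
1. Tabulate A to E by referral route, separating women who transferred from another Trust from local women. Internal self-referrals count as local. The referral-source and post code items in the baseline data set should allow this; check that the referral categories distinguish internal from external self-referral.
2. Project with the observed rate for the pilot sites (F) and the local-referral rate for the added sites: H in the Green expression, H and J in the Amber and Red expressions.
3. Beside the 48 per month threshold, report the projection with all transfers included and with all removed, as a sensitivity range.

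Keep every randomised woman in the pilot and in its analysis by allocation; only the extrapolation changes. The cost is a short addition to the criteria, one extra table from data already collected, and a possibly less favourable projected rate.

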## Secondary Outcomes

The following potential primary and secondary outcomes for a substantive trial will be feasibility-tested, and incidence rates will be used to inform power calculations for the substantive trial.

1. Admission to higher-level neonatal care, measured at 28 days following birth, as a binary (yes/no) and continuous (number of days/nights) outcome, from patients’ medical records;
2. Mode of birth measured using patient’s medical records on day of birth, as a categorial measurement to include the following categories: vaginal breech birth, forceps breech, pre-labour CS, emergency CS, cephalic vaginal birth, cephalic forceps, cephalic ventouse;
3. Composite neonatal perinatal death or serious adverse morbidity, measured at 28 days following birth, from patients’ medical notes; serious neonatal morbidity to include the following: 5 minute APGAR score <7, peripheral nerve injury present at discharge from hospital, skull fracture, spinal cord injury, admission to NICU>4 days, intubation/ventilation >24 hours, convulsions >24 hours, parenteral or tube feeding >24 hours;
4. Composite maternal death or serious morbidity, measured at 28 days following birth, from patients’ medical notes; serious maternal morbidity to include the following: postpartum haemorrhage >1000 mL, obstetric anal sphincter injury, cervical laceration involving lower uterine segment, vertical uterine incision or serious extension to transverse uterine incision, bladder, ureter or bowel injury requiring repair, dilation and curettage for bleeding or retained placental tissue, manual removal of placenta, uterine rupture, hysterectomy, vulval or perineal haematoma requiring evacuation, wound dehiscence / breakdown, wound infection requiring prolonged hospital stay / readmission / antibiotics, sepsis, disseminated intravascular coagulation;
5. Use of services following referral for breech care, to include antenatal and postnatal appointments, total time spent admitted to hospital, number of ECVs, number of ultrasound scans, and professionals present at birth, measured at 28 days following birth from patients’ medical notes;
6. Satisfaction with care, measured using previously validated survey questions with a 5-point Likert scale, at 1 month post birth
7. Experience of childbirth, measured using the ‘Childbirth Experience Questionnaire’^59,60^ at 1 month post birth

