## Masking and other measures taken to avoid bias

### Masking

It is not possible to mask participants randomised to OptiBreech Care due to our duty to describe the potential risks and benefits of a non-standard care pathway to those offered it. However, their allocation will not be indicated on their hand-held CRF or medical notes. Staff attending births and conducting subjective judgements, such as the baby’s Apgar score at birth, may know if a woman has had an attempt at ECV and is enrolled on the OptiBreech study. However, they may not know which arm the woman has been randomised to, due to the pragmatic nature of the trial. Some women will be in the cohort but not randomised, others will be randomised to one arm but choose the recommended treatment in another arm (ECV or planned VBB). Therefore, analysis by intention to treat will minimise some of the bias. All data analysis will be undertaken blind to allocation.

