# Compliance and withdrawal

## Subject compliance

This is a pragmatic trial comparing two care pathways. Rather than directly compare ECV with OptiBreech Care for a vaginal breech birth without an ECV attempt, we aim to compare a care pathway that offers one or the other as the first-line intervention. This is because the effectiveness of a care pathway depends on more than the efficacy of the intervention. Its acceptability to women and interactions with other components of the care pathway affect its clinical and cost effectiveness.

It is therefore expected that a certain percentage of women randomised to standard care will choose to plan a CS or a VBB, and a certain percentage of women randomised to OptiBreech Care will choose to attempt an ECV or plan a CS (See Figure 4: Flow of participants through OptiBreech Care trial). These acceptance rates will be evaluated as part of this study and be included in feasibility calculations.

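### The Green/Amber/Red rule compares women who accepted their allocation and were retained with a target counted in women randomised

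*Protocol*

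**What the plan says.** In the Protocol, under Green/Amber/Red Criteria for recommending a full RCT, A and C are the numbers randomised to OptiBreech care and to ECV. Then "B = number of women declining OptiBreech VBB care in favour of ECV or CS first"; D is the counterpart in the ECV arm, and E is the number lost to follow-up. The statistic is [(A−B)+(C−D)−E]/(F×G), where F is pilot sites and G is months to 104 recruits. It is multiplied by F+H for Green and by F+H+J for Amber and Red, where H and J are further sites, and compared with 48 women a month. The 48 rests on this: "Total women required for randomisation: 2280 to compare the outcome of" neonatal admission, spread over 48 months. The worked example is declared Amber.

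Other sections describe the comparison itself:

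- **Subject compliance:** "Rather than directly compare ECV with OptiBreech Care for a vaginal breech birth without an ECV attempt, we aim to compare a care pathway", defined by which option is offered first. A share of each arm is expected to choose otherwise. Acceptance rates are to enter the feasibility calculations, but how is not explained there.
- **Masking:** "Therefore, analysis by intention to treat will minimise some of the bias".
- **Statistical analysis:** neonatal admission is reported by intention to treat and is the potential primary outcome for the randomised comparison of the two offers.
- **Secondary Outcomes:** "Admission to higher-level neonatal care, measured at 28 days following birth", taken from medical records.

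**The concern.** The two sides of the rule count different things. The right-hand side is a number of women randomised. The left-hand side is a number who accepted and were retained. Under intention to treat, a woman who declines the offer is still randomised and still analysed, so she contributes to 2280.

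Non-acceptance does matter, but by another route. It shrinks the difference between the arms and so raises the number required. The rule holds that number fixed at 2280 and removes women instead.

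This is the pilot's stated tool for judging whether a full trial is feasible. It can withhold Green from a pilot whose randomisation rate meets the stated need, and it can show Amber when the arms no longer differ in the care received.

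**Working it through.** **Inputs** (Protocol, worked example): A = 52, B = 30, C = 52, D = 20, E = 2, F = 5, G = 5, H = 10, J = 25. Threshold: 2280/48 = 47.5, rounded up to 48.

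**1. The protocol's own figures.** Net count = (52−30)+(52−20)−2 = 52. Per site-month: 52/25 = 2.08. Green statistic: 2.08 × 15 = 31.2. Amber statistic: 2.08 × 40 = 83.2. Both reproduce, and the light is Amber.

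**2. The count that matches the benchmark.**

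| Women counted | Per site-month | × 15 | × 40 |
|---|---|---|---|
| Accepted and retained, 52 | 2.08 | 31.2 | 83.2 |
| All randomised, 104 | 4.16 | 62.4 | 166.4 |
| Randomised minus 2 lost, 102 | 4.08 | 61.2 | 163.2 |

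Against 48 the second and third rows are Green. The change comes from B and D; E = 2 does not alter the light.

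**3. How strict Green is at the planned pace.** Take 5 sites and 6 months (Sample size calculation) and H = 10, which is only the example's value. Green needs net/30 × 15 > 48, so net > 96. The inequality is strict, so at least 97 of 104 must be left and at most 7 women in both arms together may decline or be lost. The example has 52 (30 + 20 + 2). Counting all 104 randomised gives 104/30 × 15 = 52.0, above 48.

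**4. Blindness to contrast.** Suppose, with the example's sites and months, that B = 26 all choose ECV, D = 26 all take up OptiBreech vaginal birth, and E = 0. Each arm then receives the same mix of care, and no sample size would suffice. The net count is 26 + 26 = 52, so the rule returns 31.2 and 83.2, again Amber.

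**5. What the light should be in the example.** Let f be the fraction of the full between-pathway effect that survives in the comparison of offers. For a test of a difference, required N is roughly proportional to 1/f². If 2280 assumes f = 1, the monthly need is 47.5/f². Set against 62.4 and 166.4:

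- Green needs f > √(47.5/62.4) ≈ 0.87.
- Amber needs f > √(47.5/166.4) ≈ 0.53.
- Below about 0.53 the light is Red.

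If 2280 already allows for the dilution, the threshold stays at 48 and the light is Green.

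**The case against.** The subtraction looks deliberate, since Subject compliance says acceptance will enter the feasibility calculations. Discounting for it is a crude caution that will often err on the safe side. The light is not automatic: the Trial Steering Committee decides, with an independent statistician who receives the original data. Acceptance by arm is already a primary outcome, and setting the full-trial sample size is already an objective. All of this stands, and it limits the harm. It does not reconcile the rule with intention to treat or with the label on 2280, and the formula would still be applied as printed.

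Three stronger readings are tempting, but the document does not support them.

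- **The example ought to be Green.** That holds only if 2280 already allows for dilution, or if dilution is small. Neither is stated.
- **The example ought to be Red.** If half the decliners took the other arm's pathway, f = 1 − 0.5 × (30/52 + 20/52) ≈ 0.52. The required number would be about 8,460, against 166.4 × 48 ≈ 7,987 available. The one-half is an assumption with no basis in the text, because B and D pool caesarean with the other pathway. This formula also ignores dilution from women choosing caesarean. At a share of about 0.48 the result returns to Amber.
- **Subtracting E is simply wrong.** A woman lost only to the surveys still has a record-based 28-day outcome. However, E is not defined as survey loss, and Dropout of participants stops data collection for women who withdraw. Removing women whose outcome cannot be obtained is ordinary practice.

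**Conclusion.** The mismatch is certain and needs only the protocol. A count net of decliners is compared with a requirement for women randomised, in a trial of offers analysed by intention to treat. In the protocol's example the like-for-like figure is 62.4 (61.2 net of losses) instead of 31.2, on the other side of 48. With few decliners the two counts would agree, so the rule does not mislead for every possible result.

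The correct light for the example cannot be settled, because the effect, alpha and power behind 2280 are not given. It is Green if 2280 already allows for dilution. If 2280 assumes full contrast, it is Green only above a retained contrast of about 0.87, Amber from about 0.53 to 0.87, and Red below that. The printed Amber may therefore be right, but only by coincidence. These bounds assume a test for a difference, the 1/f² approximation and all 104 women counted.

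**What to change.** 1. Use (A+C)/(F×G) in all three rules. Subtract, once only, women whose 28-day admission outcome cannot be obtained, including withdrawals.
2. State the effect, alpha and power behind 2280, and whether it is for the diluted difference between offers. If it is not, use the observed B and D, split by the pathway actually chosen, to recompute the required number and the monthly threshold.
3. Give separation between the arms to the Trial Steering Committee as its own criterion.
4. Redo the worked example.

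The cost is a change of protocol wording and a revised example. The split of B and D needs no extra collection, since planned mode of birth, ECV attempts and mode of birth are already in the data set.
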